## Abstract

**Background:**

Major depressive disorder (MDD) is projected to rank second on a list of 15 major diseases in terms of burden in 2030. The contribution of MDD to disability and health care costs is largely due to its highly recurrent nature. Therefore, part of the efforts to reduce the disabling effects of depression should focus on preventing recurrence, especially in patients at high risk of recurrence. The best established effective psychological intervention is cognitive therapy, with indications for prophylactic effects after remission.

**Methods/Design:**

In this randomized controlled trial (cost-) effectiveness of Preventive Cognitive Therapy (PCT) after response to Acute Cognitive Therapy (A-CT) will be evaluated in comparison with Treatment As Usual (TAU). Remitted patients that responded to A-CT treatment with at least two previous depressive episodes will be recruited. Randomization will be stratified for number of previous episodes. Follow-ups are at 3, 6, 12 and 15 months. The primary outcome measure will be the time to relapse or recurrence of depression meeting DSM-IV criteria for a major depressive episode on the Structured Clinical Interview for DSM-VI Axis I Disorders (SCID-I). Costs will be measured from a societal perspective.

**Discussion:**

This study is the first to examine the addition of PCT to TAU, compared to TAU alone in patients that recovered from depressive disorder with A-CT. Alongside this effect study a cost effectiveness analysis will be conducted. Furthermore, the study explores potential moderators to examine what works for whom.

**Trial registration:**

Netherlands Trial Register (NTR): 2599, date of registration: 11-11-2010.

## Background

High prevalence, and frequent relapse and recurrence contribute to the public health significance of Major Depressive Disorders (MDD). Depression is the most disabling disorder worldwide measured in years lived with disability [1]. In various recent epidemiological studies, the annual prevalence in the general population varies from 4 % to 6 % [2, 3]. Epidemiological estimates place the lifetime prevalence of MDD at more than 16 % [4]. However, the major contribution of MDD to disability and health care costs is largely due to its highly recurrent nature. The large majority of individuals with MDD experience more than one episode and the probability of another episode increases with each relapse or recurrence [5, 6]. Reported relapse and recurrence rates for high risk groups, rise up to 60–70 % recurrence over 2 year [7, 8]. Apart from the number of previous episodes, residual symptoms after remission are risk factors for recurrence [9, 10]. Optimizing long-term outcomes is therefore an important goal in the treatment of MDD, especially for well-known high risk groups, i.e. patients with multiple previous episodes and/or residual symptoms.

We know that acute phase treatment of depression with Cognitive Therapy (A-CT) has a prophylactic effect [11]. After completing A-CT, patients are less likely to relapse than after stopping a similar course of pharmacotherapy [12]. However, recent meta-analysis showed that after remission on A-CT, many responders still have a relapse-recurrence (29 % within 1 year and 54 % within 2 years) [8]. Other studies also show that after remission a sizable number (40 %) will experience a return of symptoms after treatment [9, 13].

The most commonly used treatment to prevent relapses and recurrences is antidepressant medication (AD). However, 70–80 % of patients are not willing to take AD for a long period of time [14, 15]. Also non-adherence is common among AD-users, which is troubling as patients’ protection from recurrence ceases on discontinuation of AD and therefore increases the risk of recurrence [16, 17]. Most patients prefer psychological interventions to drug treatment, this is especially relevant in long term treatment as studies show that patients’ treatment preference is associated to compliance [18].

Jarrett and colleagues developed and tested a model of Continuation-phase Cognitive Therapy (C-CT). C-CT consists of ten sessions over a period of eight months and is provided after 20 sessions of A-CT, both provided by the same therapist. They found that C-CT reduces time to relapse and recurrence compared with an assessment-only control [19]. Responders to A-CT who received C-CT were significantly less likely to relapse (10 %) compared to those who received the assessment-only control (31 %). In the same study responders to A-CT with unstable remissions also benefited (37 % vs 62 %). Furthermore, responders to A-CT with more residual symptoms were more likely to require C-CT to avoid relapse than responders with lower or no residual symptoms [20]. Although these results are promising they are not replicated yet. Given the limited therapy resources, and the fact that remitted patients might not be motivated to an intervention that consists of eight months after remission, C-CT with fewer sessions given within a two month time-period would be desirable.

Building on this knowledge [name] developed Preventive Cognitive Therapy (PCT). PCT is a form of Cognitive Therapy aimed at treating an underlying vulnerability and thereby inducing long-term effects on depression recurrence. After remission, sequential PCT is proven effective in preventing relapse and recurrences in patients with multiple episodes over 5.5–10 years compared to treatment as usual (TAU) [7, 21, 22]. However, this study did not include patients treated with A-CT. Therefore, the (cost-) effectiveness of PCT after remission on A-CT is still unknown and the main goal of this study. PCT differs from C-CT as it is a brief intervention, only taking 8 weeks, and can be given by another therapist than the one providing A-CT. Because PCT is shorter and given within two months this might enhance possibilities for dissemination.

This study is the first to assess the (cost-) effectiveness of 8 sessions of PCT in comparison with TAU in high risk patients who remitted after receiving A-CT. A clinically relevant difference between PCT and TAU might result in enormous health effects on the population level.

### Trial objectives

In this study, the addition of PCT to TAU will be compared to TAU alone in patients that recovered from recurrent depressive disorder after treatment with A-CT. Alongside this effectiveness study a cost-effectiveness study will be done. It is hypothesized that adding PCT to TAU is clinically superior tot TAU alone in preventing relapse and recurrence of depressive disorder.

Furthermore, the study explores potential moderators to examine what works for whom. Potential mediators will also be examined to explore the working mechanism of PCT by assessing coping, social support, dysfunctional attitudes, affiliation, daily stress and functioning, and their association to risk of relapse in depression, before, during and after treatment.

## Methods/Design

### Design

In this multi-center randomized controlled trial with a follow-up of 15 months, we compare the addition of PCT to TAU in patients who recovered from depressive disorder after receiving CT, to TAU alone. An economic evaluation from a societal perspective will be performed alongside this RCT.

The target population consists of patients with a history of two or more depressions which is a group at elevated risk of relapse and recurrence of depression. This group consumes a considerable amount of healthcare mainly due to relapse rates witch rise which increasing numbers of previous episodes as identified in several studies [10].

Randomization at patient level will be undertaken by an independent researcher using a computer-generated random schedule and will be stratified by number of previous depressive episodes. The randomization is accessible solely by the independent researcher. For a Flow diagram of the assessment methods see Fig. 1.

**Fig. 1 Fig1:**
[figure not shown]
Flow-chart of the study

### The interventions

#### Acute Cognitive Therapy

All patients who enter this study have received Acute Cognitive Therapy (A-CT) during the acute phase of depression consisting of at least 8 sessions specifically designed for patients with depression. A-CT is directed at the identification of maladaptive cognitions. Each session follows a fixed structure, with agenda setting, review of homework, explanation of rationale of each session, and assignment of homework [23].

#### Treatment as usual

TAU consists of usual care that patients receive in primary care and in secondary care, after A-CT for depression. TAU may include no treatment at all or anti-depressant maintenance medication, which is in most cases provided by the general practitioner (GP). Thus, use of AD will not be an exclusion criterion. Treatment received as part of TAU will be included as covariate in the final analysis. A comparison of the intervention with TAU is relevant from a public health perspective since it would help to demonstrate the intervention’s added value over and above TAU. We will not intervene with TAU, but closely monitor healthcare utilization in TAU.

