### Secondary outcome

Secondary outcome variables are;Depressive symptom severity as measured with the HAM-D [27], Inventory of Depression Symptomatology (IDS) [28] and the Beck Depression Inventory (BDI-II) [29].Duration of relapse/recurrence.Number of relapses.Quality of life as measured by the EuroQol (EQ-5D). The EQ-5D scores will be used to calculate utilities using the Dutch tariff [30]. Quality-adjusted life-years (QALYs) will be calculated by multiplying the utility of a health state by the time spent in this health state using linear interpolation between time points. Higher QALY scores indicate higher quality of life.Health care utilization and productivity losses will be measured with an adapted version of the Trimbos Questionnaire for Costs associated with Psychiatric illness (TIC-P), a widely used health service receipt interview in economic evaluations [31]. Costs that will be included in the economic evaluation are direct medical and non-medical costs, and indirect costs. Resource utilization (GP visits, hospital days, ect.) will be valued using Dutch standard costs [32]. Using the TiC-P, both absenteeism and presenteeism (working less efficiently while at work) will be measured. Productivity losses will be valued using the friction cost method.The frequency and intensity of daily stress as measured with the Brugha and the Everyday Problem Checklist (EPCL) [33].

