### Analysis

The primary outcome measure will be the time to relapse or recurrence meeting DSM-IV criteria for a major depressive episode on the Structured Clinical Interview for DSM-VI (SCID-I). Occurrence of relapse or recurrence (current or since the last assessment point) will be assessed after 15 months, by trained psychologists who are blind to the treatment condition. Cox regression analysis will be performed. Analysis will be conducted by intention to treat, including all subjects randomized in the study, and per protocol. Statistical significance will be set at p < .05. The time (in weeks) of relapse or recurrence to Major Depression, as defined above, will be the dependent variable in survival analysis. The treatment group will be used as predictor, and the stratification variable will be used as covariate. In addition, time since previous episode and time since last treatment will be included as covariates.

In addition, we use the HAM-D, to assess the severity of depression at both time points, together with the SCID-I.

Mixed-model analysis will be used for the quantitative measures. As covariates we will use the stratification variable (number of episodes). Potential moderators to be examined include gender, residual symptoms of depression, duration of remission, duration of last episode, coping, age of onset and current use of AD.

For the economic evaluation the relationship between costs and health outcomes of the two treatment conditions will be evaluated using a societal perspective. Both a cost-effectiveness analysis with depression-free survival time as effect measure and a cost-utility analysis with QALYs as effect measure will be performed.

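### The rule to adjust for treatment received as part of TAU is not limited to treatment before randomisation and is missing from the Cox covariate list; if care after randomisation is entered, the hazard ratio may no longer be the intention-to-treat effect

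*Protocol article*

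**What the plan says.** All references are to the protocol article.

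- **Treatment as usual** sets the rule: "Treatment received as part of TAU will be included as covariate in the final analysis". It names no time point.
- The same section defines the care concerned: "TAU consists of usual care that patients receive in primary care and in secondary care, after A-CT for depression". It may be nothing at all or maintenance antidepressants. The section adds: "We will not intervene with TAU, but closely monitor healthcare utilization in TAU".
- **Trial objectives** gives the comparison: "the addition of PCT to TAU will be compared to TAU alone in patients that recovered from recurrent depressive disorder". TAU therefore runs in both arms.
- **Secondary outcome** treats care use as an outcome: "Health care utilization and productivity losses will be measured with an adapted version of the Trimbos Questionnaire". Table 1 places this questionnaire (TIC-P) at baseline and at 3, 6, 12 and 15 months.
- **Analysis** states "Cox regression analysis will be performed", by intention to treat and per protocol. It lists the terms: "The treatment group will be used as predictor, and the stratification variable will be used as covariate", and then "time since previous episode and time since last treatment will be included as covariates". Treatment received as part of TAU is not among them. Current antidepressant use appears only as a possible moderator.

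**The concern.** A covariate in a randomised comparison is safe when it is fixed before allocation. Care received after allocation is not. A patient who relapses may restart medication or return to a therapist, so the covariate is then partly a consequence of the outcome. PCT may also replace or prompt other care, so the covariate is then partly a consequence of treatment. In either case the adjusted hazard ratio no longer answers the trial's question, which is the effect of adding PCT to whatever usual care follows.

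The rule as written permits this. Four of the five planned TIC-P measurements come after randomisation, and nothing in the article restricts the covariate to the first. Because the rule and the Analysis list differ, it is also unclear which covariates the primary model contains, and the choice could be made after the data are seen.

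**Working it through.** **1. The two sections side by side**

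| Term | Treatment as usual | Analysis (Cox model) |
|---|---|---|
| Number of previous episodes (stratum) | not mentioned | yes |
| Time since previous episode | not mentioned | yes |
| Time since last treatment | not mentioned | yes |
| Treatment received as part of TAU | yes, no time point | no |
| Current antidepressant use | not an exclusion | moderator only |

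**2. The plan's own figure.** The Sample size section gives 85 per arm for a 20-point difference, one-sided alpha 0.05 and power 0.80, but no control rate. I assume 54% against 34%; 54% is the two-year relapse figure quoted in the Background.

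- Without continuity correction: n = [1.645·√(2·0.44·0.56) + 0.842·√(0.54·0.46 + 0.34·0.66)]² / 0.20² ≈ 75.1, which rounds up to 76.
- With correction: (75.1/4)·[1 + √(1 + 4/(75.1·0.20))]² ≈ 84.8, so 85.
- Dropout: 85/0.80 = 106.25, so 107 per arm and 214 in total.

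The stated size reproduces and is not in dispute. It only anchors the scenarios below.

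**3. Why the covariate can carry the outcome.** Assume a 15-month control risk of 50% and HR 0.52. The PCT risk is then 1 − 0.50^0.52 = 30.3%, a difference of about 20 points. Assume 25% of patients in both arms receive care for other reasons, and a share *a* of relapsers start care because of relapse. Then P(care | relapse) = 1 − 0.75·(1 − a), and P(care | no relapse) = 0.25.

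| a | P(care given relapse) | Care in control arm | Care in PCT arm | Gap |
|---|---|---|---|---|
| 30% | 0.475 | 36.3% | 31.8% | 4.4 points |
| 60% | 0.700 | 47.5% | 38.6% | 8.9 points |
| 90% | 0.925 | 58.8% | 45.5% | 13.3 points |

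For example, at 90% the control arm has 0.50·0.925 + 0.50·0.25 = 58.8%. The whole gap is produced by the difference in relapse, and adjusting for it removes part of the real effect.

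**4. Size with a true effect, two-sided 0.05.** Simulation with the inputs of step 3, 107 per arm, exponential times, and a fixed ever/never care term added to the Cox model. The ranges span independent runs and show simulation error.

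| a | HR without term | HR with term | Power without | Power with |
|---|---|---|---|---|
| 30% | 0.52 | 0.52–0.53 | 84–85% | 81–84% |
| 60% | 0.52 | 0.56–0.57 | 84–85% | 71–74% |
| 90% | 0.52 | 0.61–0.62 | 84–85% | 57–60% |

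**5. The same on the plan's one-sided test.** Inputs: 85 per arm, 54% against 34%, 65 weeks, 30% other care in both arms, 1,000 runs. HR is about 0.53 and power 0.84–0.86 without the term.

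- With the term, at a = 30%, 50% and 80%: HR 0.54, 0.55 and 0.60; power 0.84, 0.81 and 0.70.
- If PCT also lowers other care from 40% to 20% (a = 50%): HR 0.69, power 0.46.

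**6. No true effect (54% in both arms, a = 50%).**

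- PCT raises other care from 20% to 40%: HR about 0.85; one-sided type I error 0.196 in 1,000 runs and 0.165 in a repeat of 2,000, against about 0.04 without the term.
- PCT lowers it from 40% to 20%: HR about 1.20.

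**7. Where the bias vanishes.**

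- With a true effect, other care equal in the arms and a = 0, HR is 0.53 with and without the term.
- With no true effect, PCT lowering other care from 40% to 20% and a = 0 (60% risk in both arms), HR is about 1.01 either way. The type I error in step 6 therefore needs both routes together.

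In all these runs care itself has no effect on relapse. If it had one and PCT changed care, adjustment would also remove the part of the PCT effect that passes through care. That route is not sized here.

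**The case against.** The strongest reply is that the sentence may mean treatment at entry. TAU begins after A-CT, and patients must have been in remission for at least two months, so for many it is under way before randomisation. The only active treatment named is maintenance antidepressants. The preceding sentence says their use does not exclude a patient, and adjusting for that use would follow naturally. A baseline TIC-P exists. Moreover, the sentence speaks of the final analysis, not of the primary Cox model, and how a covariate is coded is commonly left to a full protocol or SAP that is not shown.

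Much of this stands. A reader might infer that the plan certainly adjusts for follow-up care and that the result will be biased. The article does not support that: the time point is absent, not set to follow-up. Nor does it show two declared primary models; it shows one rule and one list that do not match.

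The figures are also conditional. They assume a fixed ever/never term. With a time-dependent term, care begun after relapse would not enter the model, although care sought as symptoms build up, and any effect of PCT on care, would remain. No document gives a share of relapsers who start care, and at 30% the shift is trivial. The two-sided power figures are not on the one-sided test of the Sample size section; step 5 is.

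What does not stand is leaving the sentence alone. It is a stated rule, not an omitted detail, and the monitoring sentence and the secondary outcome both point to care during the trial. A baseline reading would still leave the term missing from the Analysis list.

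**Conclusion.** The point holds as a conditional one. The rule permits adjustment for a post-randomisation variable that the trial also lists as an outcome, and it does not match the Cox covariates under Analysis. The mismatch needs no assumption.

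The bias needs two conditions: care after randomisation is entered, and that care depends on relapse or on PCT. Under a fixed ever/never term, the loss runs from negligible to a serious loss of power as the assumed share of relapsers starting care rises from 30% to 90%. The error can also favour PCT: about 0.2 one-sided type I error when half of relapsers start care and PCT doubles other care use. These are illustrations over assumed patterns, not predictions for this trial. If only baseline treatment is meant, the adjustment is harmless and only the wording needs repair.

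**What to change.** Reword the sentence under Treatment as usual so that the primary Cox model adjusts only for variables fixed before randomisation: the stratification variable, time since previous episode, time since last treatment and, if wanted, antidepressant use at baseline. Keep that single list under Analysis and refer to it from Treatment as usual.

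Report TAU received during follow-up descriptively by arm and use it in the cost analysis. Any other use belongs in a sensitivity or mediation analysis labelled as such, with the timing of care relative to relapse stated.

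The cost is a few lines of protocol or SAP wording, settled before the data are seen. No new data are needed, since TIC-P is already taken at baseline, and the sample size does not change.

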#### Preventive Cognitive Therapy

After response to A-CT, there will be a minimum two month waiting period before PCT will start. PCT consists of eight individual sessions once a week, offered as sequential treatment after response to A-CT. PCT is an adapted type of CT specifically developed to prevent relapse in recurrent depression. Similar to regular CT, each PCT session follows a fixed structure, with agenda setting, review of homework, explanation of rationale of each session, and assignment of homework [24].

PCT differs from A-CT in several aspects. Unlike A-CT, PCT is not primarily directed toward modifying negative thoughts. Instead, it starts with the identification of negative thoughts and dysfunctional attitudes and beliefs, aided by a self-report questionnaire with examples of attitudes and specific techniques such as the downward arrow technique. The focus of treatment is then directed on examining these attitudes using different cognitive techniques such as Socratic questioning and identification of positive phantasy attitudes. Moreover, patients are encouraged to practice with alternative attitudes in the final sessions. In addition, unlike with traditional A-CT, specific attention will be paid to enhancing the memory and retrieval of positive experiences and making a personal prevention plan [21]. A specific manual for the client and therapist has been published describing the structure of the treatment [24].

### Therapists

Therapists in the PCT condition are trained psychologists who are specialized in CBT. They will receive a one day training in PCT from the author of the PCT protocol that is used in this study [24]. During the study the therapists participate in regular supervision groups led by the trainer, as well as peer supervision groups led by the principal investigator. Regular supervision will be held once a week, the peer supervision once every four months. The therapists who perform the PCT are not the same therapists that provided the A-CT.

### Sample size

In total, 214 patients will be recruited. This sample size is needed to detect a difference in the primary outcome (cumulative proportion of relapse/recurrence rates over 15 months) of at least 20 % between the conditions in a 1-sided test at alpha = 0.05 and a power of (1-beta) = 0.80. For this we need 85 participants in each condition. Allowing for a drop out of 20 % over the two years, we need to include 107 participants in each condition at baseline.

